# Stereotactic body-radiotherapy boost dose of 18 Gy vs 21 Gy in combination with androgen-deprivation therapy and whole-pelvic radiotherapy for intermediate- or high-risk prostate cancer: a study protocol for a randomized controlled, pilot trial

**DOI:** 10.1186/s13063-018-2574-y

**Published:** 2018-04-02

**Keywords:** External-beam radiotherapy, Prostate cancer, Stereotactic radiotherapy boost

## Abstract

**Background:**

Combination therapy using external-beam radiotherapy (EBRT) with a brachytherapy boost has demonstrated superior biochemical control than dose-escalated EBRT alone. Whereas brachytherapy is disadvantageous because it is an invasive procedure, stereotactic body-radiotherapy (SBRT) using CyberKnife could emulate the dose distribution of brachytherapy and is a non-invasive and safe modality to control intra-fractional movement. We therefore adopted SBRT using CyberKnife as a boost therapy after whole-pelvic radiotherapy (WPRT).

**Methods/design:**

In this prospective, randomized, single-center, pilot study for intermediate- and high-risk prostate cancer without nodal or distant metastasis, after androgen-deprivation therapy and WPRT, patients will be randomized to one of two SBRT boost regimens, i.e., 18 or 21 Gy administered in three fractions every other day.

**Discussion:**

The aim of this trial is to evaluate acute toxicities using both physician- and patient-reported outcomes and short-term biochemical control with SBRT boost following WPRT. Additionally, chronic toxicities and long-term biochemical control will be evaluated as secondary endpoints in this trial. Based on the generated results, we will plan the full-scale phase II study for selecting the SBRT boost dose.

**Trial registration:**

ClinicalTrials.gov, ID; NCT03322020. Retrospectively registered on 26 October 2017.

**Electronic supplementary material:**

The online version of this article (10.1186/s13063-018-2574-y) contains supplementary material, which is available to authorized users.

## Background

High-dose external-beam radiotherapy (EBRT) with a prescription dose of 76–80 Gy is the current standard treatment for intermediate- and high-risk prostate cancer [1–3]. Recently, some studies have reported that combination therapy using EBRT with a brachytherapy boost demonstrated superior biochemical control than dose-escalated EBRT alone [4–6]. However, brachytherapy has several disadvantages including invasiveness, the need for anesthesia, insertion of multiple catheters, pain control, and hospitalization. Among the several approaches to replace brachytherapy boost with non-invasive EBRT boost techniques, stereotactic body-radiotherapy (SBRT) boost using the CyberKnife robotic radiosurgery system (Accuray Incorporated, Sunnyvale, CA, USA) is one of them. A previous trial reported that dose distribution with CyberKnife was comparable to that of brachytherapy [7]. One other advantage of CyberKnife over other SBRT delivery systems, such as volumetric modulated arc therapy, is intra-fraction motion control.

With this rationale in mind, whole-pelvic radiotherapy (WPRT) followed by SBRT boost using CyberKnife anticipates that biochemical control will be superior to the conventional high-dose EBRT. In addition, medical expenses will be lower because of a shorter total treatment time. Traditional fraction size has been 1.8–2 Gy; therefore, the duration of EBRT is 8–9 weeks. A longer EBRT is a heavy burden for both patients and the health care system. Because prostate cancer seems to have greater sensitivity to higher doses per fraction than that of organs nearby, [8] increasing the fraction size, called hypofractionation, has been adopted for prostate cancer [9, 10]. However, the implementation of hypofractionation with WPRT is challenging because of the concern of toxicity. However, administration of SBRT as boost therapy after WPRT can shorten the total treatment period to approximately 5 weeks. Several retrospective studies have assessed the clinical outcomes of WPRT with 45-Gy administered in 25 fractions, followed by a CyberKnife boost of 18–21 Gy in three fractions and demonstrated feasibility of the SBRT boost after WPRT [11, 12]. However, the boost dose and other modalities used in combination, such as androgen-deprivation therapy (ADT), varied among the patient population.

This prospective, randomized, single-center trial evaluates the acute toxicities and short-term control of prostate-specific antigen (PSA) of combination treatment including ADT, WPRT, and an SBRT boost. This trial uses two SBRT boost dose regimens, 18 and 21 Gy, both administered in three fractions. Based on the results of the study, we will design the full-scale phase II study for selecting the appropriate SBRT boost dose.

## Methods/design

### Recruitment and study design

This prospective, randomized, single-center, pilot study on intermediate- and high-risk prostate cancer patients is ongoing at Asan Medical Center. Patients are randomized into two groups with a 1:1 allocation using blocked randomization, and the random block size is 4. The randomization sequence is generated by the clinical research nurse using Excel software. The allocation sequence is concealed from the primary investigator who enrolls the patients using the Excel file locked with a password. Also, the file is saved in a computer located in the place that the primary investigator cannot approach. One group will receive a CyberKnife SBRT boost dose of 18 Gy administered in three fractions (18-Gy group), and the other group will receive a CyberKnife SBRT boost dose of 21 Gy administered in three fractions (21-Gy group).

As shown in Fig. 1, all patients will first receive ADT. Several studies strongly support the use of ADT in addition to EBRT, long-term (i.e., 2–3 years) ADT for high-risk patients [13, 14] and short-term ADT (4–6 months) for the intermediate group [15, 16]. Risk group definition is based on the current National Comprehensive Center Network guidelines (https://www.nccn.org/professionals/physician_gls/pdf/prostate.pdf). Informed consent of patients is mandatory before recruitment and is obtained from the radiation oncologists. Three months after the start of ADT, WPRT (44 Gy in 20 fractions) with intensity-modulated radiotherapy (IMRT) will be initiated. Next, CyberKnife boost will be implemented. Since the primary investigator has to confirm the plan for CyberKnife boost, the blinding is not possible afterward.

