### Statistical analysis

The present study is being performed as a purely exploratory pilot study; therefore, by calculation for statistical analysis, a total 15 patients in each treatment group is considered as an appropriate sample size. Comparison of the treatment two groups will be conducted using the chi-square test or Fisher’s exact test. Biochemical recurrence-free survival (BCRFS) will be calculated from the ADT start date using the Kaplan-Meier method. Descriptive statistics of all analyzed parameters will be provided, whenever appropriate.

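### With one block size of 4 and an enrolling investigator who learns each arm, past allocations can reveal upcoming ones if randomisation follows pelvic radiotherapy

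*Protocol article*

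**What the plan says.** All of the following is from the protocol article.

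- **Recruitment and study design.** The trial has a single centre. "Patients are randomized into two groups with a 1:1 allocation using blocked randomization, and the random block size is 4". The list is made by someone other than the enroller: "The randomization sequence is generated by the clinical research nurse using Excel software". Concealment is described as "The allocation sequence is concealed from the primary investigator who enrolls the patients using the Excel file locked with a password", with the addition that "the file is saved in a computer located in the place that the primary investigator cannot approach". The same investigator later learns the arm: "Since the primary investigator has to confirm the plan for CyberKnife boost, the blinding is not possible afterward". This section gives no time for randomisation.
- **Abstract, Methods/design.** Patients are randomised to a boost regimen after ADT and whole-pelvic radiotherapy (WPRT).
- **Data collection and follow-up period.** The boost plan is confirmed, and blinding ends, in the fourth week of radiotherapy.
- **Treatment implementation and Exclusion criteria.** ADT starts 3 months before WPRT. Recent ADT excludes a patient, so enrolment must come before trial ADT.
- **Statistical analysis.** The plan is for "a total 15 patients in each treatment group", 30 in all.
- **Trial status.** Recruitment is not complete.

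**The concern.** Concealment has two parts: the list must not be readable, and the next assignment must not be deducible. The plan secures the first. For the second, a reader who knows the block size and the arms already given can work out the rest of a block. Here the block size is published, there is one centre, and the enrolling investigator eventually sees every arm.

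What can be steered depends on timing. If randomisation follows WPRT, the patient is already enrolled and treated, so entry to the trial is no longer open to selection. Three things are still open or known just before the boost:

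- Weekly toxicity during WPRT has been recorded.
- Dropout for medical issues is a matter of judgement (Dropout criteria).
- Radiotherapy may take up to 10 weeks, against about 5 expected (Treatment implementation; Background), so the order of patients can shift.

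A patient with marked WPRT toxicity could be delayed or dropped when a particular arm is predicted. That would bear directly on acute toxicity, a primary endpoint. With 15 per arm, one patient moves a toxicity rate by 1/15 = 6.7 percentage points, and the results are meant to inform a phase II dose-selection study.

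**Working it through.** **Inputs.** Allocation 1:1 and a single block size of 4 (Recruitment and study design); 30 patients (Statistical analysis). Assumption: one unstratified list. The article mentions no strata, but the full protocol is not shown. The wording about a random block size gives only one value, so it is read as fixed.

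**Every earlier arm known.** A block has C(4,2) = 6 equally likely orders.

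- Certain assignments: places 1 and 2 never; place 3 when the first two agree (2/6 = 1/3); place 4 always. Per block: 1/3 + 1 = 4/3. Thirty patients make 7 full blocks plus 2 places: 7 × 4/3 + 0 = 9.33, and 9.33/30 = 31.1%.
- Correct guesses, always naming the arm that is behind: 1/2 + 2/3 + 2/3 + 1 = 17/6 per block. Over 30: 7 × 17/6 + (1/2 + 2/3) = 21.0, and 21.0/30 = 70.0%.

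**Recent allocations still unknown.** The same enumeration, with the k most recent arms hidden:

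| k | certain | guessed correctly |
|---|---|---|
| 0 | 31.1% | 70.0% |
| 1 | 7.8% | 57.8% |
| 2 | 0% | 53.9% |
| 3 or more | 0% | 50.0% |

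For k = 1: certain 7 × 1/3 = 2.33 of 30; correct 7 × (1/2 + 1/2 + 2/3 + 2/3) + 1 = 17.33 of 30.

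**Which row applies.**

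- *Randomisation after WPRT (abstract).* The arm is learned close to when it is assigned, so k = 0 or 1.
- *Randomisation at enrolment.* The arm is learned after 3 months of ADT plus about 4 weeks of radiotherapy, roughly 4 months. The number enrolled within that lag is 4 × 30/T for an accrual period of T months. The article gives no T, so these are assumed values: 12 months gives 10, 24 gives 5, 36 gives 3.3, 48 gives 2.5 and 60 gives 2. Guessing is therefore near chance unless accrual takes about 4 years or more.

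**Timing set side by side.** WPRT is 20 weekday fractions, or 20/5 = 4 weeks. Confirmation of the boost plan in the fourth week of radiotherapy reveals the arm while WPRT is only just finishing. Randomisation strictly after WPRT does not fit this; randomisation shortly before plan confirmation would.

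**Effect of varied blocks.** Thirty allocations were simulated with all earlier arms known. Blocks of 4, 6 and 8 drawn at random give a best-guess rate of about 68%. Certain assignments are near 0: about 2% even if the guesser knows which sizes are in use, rising to about 6% if the list is also forced to close at exactly 30. Blocks of 2, 4 and 6 forced to close at 15/15 leave the best-guess rate at about 70.6%, no better than fixed blocks of 4.

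**The case against.** **The lag protects.** The 31% and 70% hold only when every earlier arm is known. This stands. If patients are randomised at enrolment, the 4-month lag brings guessing close to chance under most plausible accrual rates. The statement that assignments are predictable must therefore be conditional.

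**The worst case rests on one phrase in the abstract.** This also stands in part, since the fourth-week unblinding does not fit randomisation strictly after WPRT. But randomisation just before plan confirmation fits both in substance and leaves the same exposure, and no section says that it happens at enrolment.

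**Varied blocks barely change guessing.** This is correct. Naming the arm that is behind needs no knowledge of block size. The gain is in certain assignments, not in the best-guess rate.

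**Stronger readings that the article does not support.**

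- *Selective entry to the trial.* This needs randomisation at enrolment, which is where the lag protects.
- *Biased contouring or grading in the blind weeks.* The boost volume is the one drawn for WPRT, and both arms receive the same treatment until the boost. Later grading is openly unblinded.
- *A failure to reach 15 per arm.* Since 30/4 = 7.5 blocks, a 16/14 split has probability 2/6 = 1/3, but nothing worse is possible. In an exploratory pilot with no stated power target, this is immaterial.

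**Conclusion.** The point holds conditionally. One published block size at a single centre, with an enrolling investigator who learns each arm, leaves allocations open to deduction however well the list is locked. If randomisation follows WPRT, between 7.8% (one recent arm unknown) and 31.1% (none unknown) of the 30 assignments are certain, and 57.8% to 70.0% can be guessed. The consequence is then possible steering of delay or dropout before the boost, not selection into the trial. If randomisation is at enrolment, the exposure is small unless accrual is slow. These figures assume one unstratified list and a fixed block of 4. Nothing suggests that steering has occurred. For an exploratory pilot this is worth correcting while recruitment is open, because the change is cheap; it does not invalidate the design.

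**What to change.** 1. For the remaining patients, have the research nurse generate a new list with undisclosed, randomly varied block sizes that avoid blocks of 2, for example 4, 6 and 8. Do not force the list to close at exactly 15/15, since that makes the last assignments deducible again.
2. Release each allocation only after the patient's registration for the boost is recorded. This limits what can be done with a guess, which varied blocks alone do not.
3. State once when randomisation takes place, and reconcile the abstract, Recruitment and study design, and Data collection and follow-up period on it.

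The cost is a new list, a sentence or two in the protocol, and slightly looser balance between arms during accrual.

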### Treatment implementation

ADT will be initiated 3 months before WPRT (Fig. 1). In the intermediate-risk group, ADT will be administered for 6 months, whereas in high-risk group, long-term ADT for 2–3 years will be administered. Administration of antiandrogens and/or luteinizing hormone-releasing hormone agonists is allowed for patients in this study.

Before computed tomography (CT) for treatment planning, an experienced radiologist will insert three gold intra-prostatic fiducial markers via endorectal sonography for CyberKnife tracking. One week later, enhanced CT scans with a slice thickness of 2.5 mm will be obtained in all patients who will have empty bladders and rectal balloons in place. Participants should be in a relaxed supine position facilitated by an ankle pillow. Afterwards, a radiation oncologist will delineate organs-at-risk (OAR) and target volumes. If available, fusion with diagnostic magnetic resonance imaging (MRI) is recommended. Gross target volume (GTV) includes whole prostate glands, involved extraprostatic tissues, and any suspicion of involvement of the seminal vesicles. If seminal vesicle invasion is excluded definitely, they will not be included in the GTV calculation. Clinical target volume (CTV) includes regional nodal areas including obturator, external/internal iliac, and presacral lymphatic areas. Planning target volume (PTV) is expansion of CTV margins by 5 mm, except for the posterior 3-mm margin for rectal sparing. PTV must be irradiated with ≥ 95% of the prescription dose. OAR includes the rectum, bladder, and femoral heads, and all are contoured according to the Radiation Therapy Oncology Group guidelines [18]. IMRT will be used, and the dose regimen will be 44 Gy in 2.2-Gy fractions every weekday. Dose constraints are as follows: (1) bowel (small and large), 30% of the entire bowel volume must not receive more than 40 Gy; (2) rectum, 60% of the volume must receive ≤ 40 Gy; (3) bladder, 35% of the bladder volume must receive ≤ 45 Gy; (4) femoral heads, 15% of the femoral head volume must receive < 35 Gy. WPRT will be initiated within 10 days after the day of CT for treatment planning. For image guidance, daily cone-beam CT will be used. Patients will be asked to empty their bladder before each fraction, while there will be no routine bowel preparation.

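### Allocation and the stated arm comparison ignore risk group, which sets whether PSA at the 4-month visit is read on or off ADT; the cost is precision and interpretability, not bias

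*Protocol article*

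**What the plan says.** **Allocation.** Recruitment and study design: "Patients are randomized into two groups with a 1:1 allocation using blocked randomization, and the random block size is 4". The section goes on to who generates the sequence and how it is concealed, but names no stratification factor. The same section says that both risk groups are enrolled: "pilot study on intermediate- and high-risk prostate cancer patients is ongoing".

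**ADT by risk group.** Treatment implementation: "In the intermediate-risk group, ADT will be administered for 6 months, whereas in high-risk group, long-term ADT for 2–3 years will be administered". ADT starts 3 months before whole-pelvic radiotherapy.

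**Timing of PSA.** Data collection and follow-up period schedules visits 1 and 4 months after radiotherapy, with PSA among the data recorded. Radiotherapy is expected to take about 5 weeks (Background) and may not exceed 10 (Treatment implementation).

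**Endpoint.** Short-term biochemical control is one of two primary endpoints, with no time point given. Recurrence is a PSA rise of 2 ng/ml or more above nadir (Assessment of primary and secondary endpoints).

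**Analysis.** Statistical analysis: "Comparison of the treatment two groups will be conducted using the chi-square test" or Fisher's exact test, with no stratification or covariate. BCRFS is estimated by Kaplan-Meier from the start of ADT. On size, "a total 15 patients in each treatment group is considered as an appropriate sample size", and on status, "The present study is being performed as a purely exploratory pilot study".

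**The concern.** Risk group is more than a general prognostic factor here. The protocol itself ties it to a co-treatment that acts on PSA. If ADT has ended in one risk group and continues in the other when PSA is measured, the PSA result in each arm depends partly on that arm's risk mix, whatever the boost dose. Nothing in the allocation holds the mix equal, and the stated test does not account for it.

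The Background faults earlier boost studies because co-treatments such as ADT varied between patients. This trial also varies ADT between patients, and neither its allocation nor its stated comparison takes that into account. The results are to be used in designing the phase II study that will select the boost dose, so a misread arm difference could be carried forward.

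**Working it through.** **Inputs from the article.** 1:1 allocation in blocks of 4; 15 per arm, 30 in total; ADT start 3 months before radiotherapy; ADT for 6 months or 2–3 years; radiotherapy about 5 weeks, at most 10; PSA at 1 and 4 months after radiotherapy.

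**Assumptions.** High-risk share 30–70% (not stated in the article). All PSA-control rates below are illustrations.

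**The plan's own figure.** The article says that 15 per arm was reached "therefore, by calculation for statistical analysis" but gives no alpha, power, effect or rates, so the figure cannot be reproduced. The point does not depend on it.

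**Step 1: ADT status at the PSA visits.** Months from ADT start, with 1 month = 30.4375 days = 4.348 weeks. End of radiotherapy = 3 + weeks/4.348.

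| Radiotherapy | End | 1-month visit | 4-month visit |
|---|---|---|---|
| 5 weeks | 3 + 1.15 = 4.15 | 5.15 | 8.15 |
| 10 weeks | 3 + 2.30 = 5.30 | 6.30 | 9.30 |

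Intermediate-risk ADT ends at month 6, high-risk ADT at months 24–36. At the 4-month visit intermediate-risk patients are 8.15 − 6 = 2.15 to 9.30 − 6 = 3.30 months past ADT, and high-risk patients are still on it. At the 1-month visit both groups are on ADT unless radiotherapy takes more than 6 − 3 − 1 = 2 months, that is 2 × 4.348 = 8.7 weeks.

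**Step 2: chance imbalance in risk mix.** Seven full blocks cover 28 patients. The last two patients come from an incomplete block and fall in the same arm with probability 1/3. The arms are therefore 15 and 15 with probability 2/3, and 14 and 16 with probability 1/3. Without stratification, the numbers of high-risk patients in the arms are independent binomials, so P = (2/3)·P(15 v 15) + (1/3)·P(14 v 16).

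| High-risk share | P(difference ≥ 20 points) | P(difference ≥ 30 points) |
|---|---|---|
| 30% or 70% | (2/3)(0.318) + (1/3)(0.230) = 0.289 | 0.073 |
| 33% or 67% | (2/3)(0.332) + (1/3)(0.245) = 0.303 | 0.081 |
| 50% | (2/3)(0.362) + (1/3)(0.276) = 0.333 | 0.099 |

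Simulation of 20,000 trials per scenario agrees: 0.30 to 0.33 for 20 points and 0.08 to 0.10 for 30 points, for shares of 33–67%. With blocks of 4 run within each risk group, no simulated trial reached 20 points. The mean absolute difference fell from about 14 points to about 3, and the largest seen was 12.5.

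**Step 3: what an imbalance does to the arm difference.** With no dose effect, shift = (gap in control between risk groups) × (imbalance).

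- Gap of 5 points, as might apply to early nadir-plus-2 recurrence: 0.05 × 0.20 = 1 point; 0.05 × 0.33 = 1.7 points. One patient of 15 is 6.7 points.
- Gap of 60 points, a strong illustration such as a PSA-level threshold: 0.60 × 0.20 = 12 points.

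**Step 4: validity and precision.** Take half the patients as high risk, control of 30% and 90% in the two groups, and no dose effect. In 6,000 simulated trials the unstratified design gave a mean arm difference of about 0 and a Fisher rejection rate of about 0.02, below the nominal 0.05. For precision:

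- SD with risk mix left to chance: √(2 × 0.6 × 0.4/15) = 0.179.
- SD with risk mix balanced: √((0.3 × 0.7 + 0.9 × 0.1)/15) = 0.141.

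Simulation gave 0.18 and 0.14. With smaller gaps around 70% control the gain shrinks: from 0.167 to √((0.8 × 0.2 + 0.6 × 0.4)/15) = 0.163 for a 20-point gap, and to √((0.9 × 0.1 + 0.5 × 0.5)/15) = 0.151 for a 40-point gap.

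**The case against.** **Randomization makes the unadjusted test valid.** This stands. A reader might infer that the design is biased or produces false positives. Step 4 shows neither: the expected arm difference is zero and type I error is not inflated.

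**Large spurious differences in early control are not credible.** This stands for the stated recurrence definition. A reader might assume that control differs by 20–40 points between risk groups and read off shifts of several points. But the Discussion reports 5-year BCRFS of 84–89% in the arms of the cited phase III boost trial, that is 11–16% failing. Even with every failure in one half of the patients, the gap at five years could not exceed 22–32 points. At month 8, with high-risk patients still on ADT, a 5-point gap is nearer the mark (an assumption), and its effect is well under one patient. The argument is weaker for PSA level or nadir, which the article leaves open: the Background speaks of short-term control of PSA, and the primary endpoint has no time point.

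**The point does not reach every primary outcome.** This also stands. A reader might extend it to all early PSA or to acute toxicity. On the 5-week schedule both groups are on ADT at 1 month, and nothing in the article links acute toxicity to risk group.

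**A stratified analysis may sit in a plan that is not shown.** This stands in part. The article does not rule out tables by risk group, and it promises descriptive statistics. But it describes the allocation specifically, without a stratification factor, and names the between-arm test.

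**A small exploratory pilot need not stratify.** Unstratified blocking is a defensible choice in 30 patients, and this limits the severity. It does not remove the case for a cheap change, since 30 patients is where chance imbalance is most likely.

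**Conclusion.** The point holds as a matter of precision and interpretability. Both the allocation and the stated comparison ignore a binary factor, known at entry, that determines whether PSA at the 4-month visit is read on or off ADT. There is roughly a 30% chance (29–33%, for an assumed high-risk share of 30–70%) that the arms differ by at least 20 points in that factor.

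The consequence is confined to the 4-month and later PSA comparisons. It matters most for PSA level or nadir, and for later BCRFS, where high-risk patients remain on ADT for the first 2–3 years of a curve that starts at ADT initiation. How much precision is lost depends on the gap between risk groups, which the article does not give. It is a worthwhile improvement while recruitment is open, not a flaw that invalidates the trial.

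**What to change.** 1. **Allocation.** For patients still to be enrolled (Trial status says recruitment is not complete), run the blocks of 4 separately for intermediate- and high-risk patients.
2. **Analysis.** Report PSA outcomes by arm within risk group and compare the arms within risk group, for example with an exact Cochran-Mantel-Haenszel comparison stratified by risk group. The two changes belong together. In the 30%/90% illustration, stratified allocation followed by the unstratified Fisher test rejected in only 0.3% of null trials, against about 2% with unstratified allocation, so the unstratified test would waste the gain.

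**Cost.** No extra patients and no new data, since risk group already decides ADT length. A second locked sequence is needed. If all 30 were allocated this way, the remainders after full blocks in the two strata would be 0 and 2, 1 and 1, or 3 and 3, so final arm sizes would differ by at most 2, as under a single list. Separate blocks fill more slowly, and the enrolling investigator learns each allocation when the boost plan is confirmed, so later assignments within a fixed block of 4 become somewhat easier to predict. The balance gained covers only the remaining enrolment, and the stratified test adds little if events are few.
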